**S2 Protocol. Protocol (in English).**

Clinical study protocol

Clinical study title: Comparison of the effects of oral hygiene instruction and periodontal treatment in patients with type 2 diabetes mellitus
（Comparison of the effects of oral hygiene instruction and periodontal treatment on patients with type 2 diabetes mellitus）

Principal investigator: [name]

Department of Preventive Dentistry, Okayama University Graduate School of Medicine, Dentistry and Pharmaceutical Sciences, Okayama, Japan

[name]

Telephone no. (ext.): [contact] [name]

[contact]

E-mail: [contact]

Emergency contact (medical office number): [contact]

Planned duration of study: March 1, 2014 – March 31, 2016.

Comparison of the effects of oral hygiene instruction and periodontal treatment in

patients with type 2 diabetes mellitus

Study protocol

1. Background

The “Basic Matters Related to Dental and Oral Health Promotion” are based on the “Dental and Oral Health Promotion Law” enacted in August 2012. It describes the relationship between oral status and general health, between dental diseases and lifestyle habits, and between oral health and medical expenses, as well as the promotion of research on prevention and treatment methods that are effective from their relation to dentistry. Innovation is needed especially in dental-medical collaborative model projects for diabetes patients, as the close relationship between periodontal disease and diabetes continues to be elucidated.

2. Study objectives and necessity

In this study, type 2 diabetes patients being treated on an outpatient basis at Okayama University Hospital will be divided into two groups, an oral hygiene health instruction group (given guidance on plaque control only) and a non-surgical periodontal treatment group (given guidance on plaque control and periodontal treatment). The purpose of this study is to compare the results of tests (clinical and blood biochemistry tests) performed 6 months after the conclusion of periodontal treatment (including full mouth scaling and root planing), and the effects on changes in quality of life (QOL) in these two groups.

The current status of medical-dental collaboration for diabetes patients consists mainly of cooperation between medical and dental institutions by referring patients to each other, and the clinical significance is unclear. The results of this study will give clinical significance to the content of such collaboration (providing support for the improvement in diabetes status from periodontal treatment). This is promising for use as evidence for the introduction of periodontal treatment into health care services covered by health insurance, such as “Dental support additions to diabetes and other patients (provisional)” in future Health, Labour and Welfare administrations.

3. Summary of pharmaceuticals and medical equipment

Not applicable.

4. Subjects

(1) Inclusion criteria:

Patients who meet all of the following criteria will be included as subjects:

1. Currently receiving treatment for type 2 diabetes
2. Capable of participating in the study for 6 months
3. Supported by medical insurance
4. 30 years or older at the onset of study (at the time of informed consent)
5. Consenting patients (Patients who voluntarily provide written consent after receiving a full explanation and fully understanding participation in the study)
6. Outpatients

(2) Exclusion criteria:

Patients who are incompatible for any of the following reasons will be excluded:

- - - - 1. Undergoing dental treatment
        2. Pregnant or possibility of being pregnant
        3. Determined as unsuitable subjects (Other patients judged by the principal investigator or a co-investigator to be unsuitable as subjects)

5. Explanation of study to subjects and obtaining consent

Patients will be given an informed consent form approved by the Ethics Committee, Okayama University Graduate School of Medicine, Dentistry and Pharmaceutical Sciences and Okayama University Hospital, and the study will be fully explained both orally and in writing. Written consent will then be obtained at the discretion of the patients. In the event of a change in the protocol or other matters that may affect consent, such information will be provided to patients promptly and the decision on whether to participate in the study will be confirmed again. At the same time, the informed consent form or other relevant forms will be revised with advance approval by the same Ethics Committee, and consent will again be obtained from patients.

6. Study methods

The following are provided:

(1) Study type/design

Randomized controlled study

(2) Study outline

| **Assessment**  • Primary endpoint: HbA1c  • Secondary endpoints: periodontal status, blood sugar, oxidative stress, and QOL  **Oral hygiene instruction group**  Receives oral hygiene instruction  Recruitment of study participants  **Non-surgical periodontal treatment group**  Receives oral hygiene instruction + scaling and root planning, professional toothbrushing and mechanical tooth cleaning |
| --- |

Figure. Study flow chart

Type 2 diabetes patients in the Nephrology, Diabetology and Endocrinology Department of Okayama University Hospital who consent to participate in the study will be introduced to the Department of Preventative Dentistry outpatient clinic. One member of the research group will separate patients into two groups, the oral hygiene instruction group and the non-surgical periodontal treatment group, using a table of random numbers (the patients will be asked not to inform the examiners of the group to which they are assigned). Thereafter, two dentists blinded to the group assignments will conduct periodontal examinations. Other dentists will then be in charge of oral hygiene instruction and periodontal treatment. For the periodontal examination, calibration will be repeated in advance until the kappa value (a reliability assessment index) exceeds 0.8 for inter- and intra-operator agreement.

The periodontal examination includes probing pocket depth, clinical attachment level (distance from the border between the tooth crown and root to the bottom of the periodontal pocket), bleeding on probing (whether bleeding is seen when the periodontal pocket depth is measured), and the degree of plaque buildup.

Blood tests are routinely conducted as part of regular medical examination in the Nephrology, Diabetology and Endocrinology Department (and will be arranged so that examinations are conducted in the Nephrology, Diabetology and Endocrinology Department and the Department of Preventive Dentistry on the same day). In blood tests, glycated hemoglobin (HbA1c) and glycated albumin will be assessed. Remnant blood from examinations (blood that would otherwise be disposed of as medical waste) will be used by the research group for measurement of the oxidative stress balance.

Some of the above examinations will be performed a total of three times: at the start of the study, after 3 months, and after 6 months. Periodontal treatment will be completed by 2 months from the start of the study. Oral hygiene instruction will be provided to both groups at the start of the study, after 3 months, and after 6 months. In cases where there is a change in diabetes treatment during the study period, the details will be recorded.

(3) Planned duration of subject participation

Six months.

(4) Usage, dosage and administration period of study drugs

Not applicable.

(5) Study drug dosage form/content, properties, packaging, labeling, and storage

Not applicable.

(6) Provisions regarding concomitant medication (therapy)

Not applicable.

(7) Drug withdrawal method

Not applicable.

(8) Management and delivery procedures for study drugs

Not applicable.

(9) Drug administration guidance information

Not applicable.

(10) Case enrollment, allocation

Subject enrollment:

The principal investigator or a co-investigator will: 1) obtain written consent; 2) write the date on which consent was obtained and the items needed to link the subjects to the subject identification code on the subject identification code list kept by the principal investigator; 3) submit the case report form using the subject identification code to the study office (medical office for the Department of Preventive Dentistry); and 4) report immediately in the event of consent withdrawal, discontinuation, or dropout.

Subject allocation:

The subjects will be allocated to the treatment groups with a table of random numbers. Using a stratified block randomization allocation method, adjustments will be made according to baseline serum HbA1c (≥8% and <8%), whether a patient is receiving insulin treatment, and types and number of drugs (≤2 or ≥3) a patient is taking.

(11) Handling at completion of study

After the completion of the study, the principal investigator will provide the treatment he considers to be the most appropriate for each subject, including treatment based on the findings obtained in this study.

7. Assessments

(1) Primary endpoint

Serum HbA1c (National Glycohemoglobin Standardization Program [NGSP] value)

(2) Secondary endpoints

Periodontal status (number of teeth present, probing pocket depth, clinical attachment level, bleeding on probing, Plaque Control Record)

Hematological index (glycated albumin)

Blood biochemical index (oxidative stress balance)

QOL

(3) Safety assessment

Not applicable.

8. Observation and test items

(1) Patient characteristics: Chart number, patient’s initials, sex, date of birth, race, inpatient or outpatient, height, weight, complications, past medical history, history of present illness, previous treatment, and other.

(2) Confirmation of subjective and objective symptoms: Confirmation by interview (with reference to the symptom diary if available).

(3) Blood test: Same test items as in regular medical examination.

(4) Blood biochemistry test: Same test items as in regular medical examination. Factors associated with oxidative stress will also be assessed to confirm the relationship between oral health and whole body status.

(5) Periodontal examination: Number of teeth present, probing pocket depth, clinical attachment level, bleeding on probing, and Plaque Control Record.

(6) Questionnaire survey on QOL.

Table. Study Schedule

| Item | | Study initiation | Period of periodontal treatment | Observation period | |
| --- | --- | --- | --- | --- | --- |
| Timing | | Week 0 | Less than 2 months | After 3 months | After 6 months |
| Examination | | Examination 1 | Examination 2–5 | Examination 6 | Examination 7 |
| Consent obtained | |  |  |  |  |
| Confirmation of patient characteristicsa | |  |  |  |  |
| Oral hygiene instruction | |  |  |  |  |
| Periodontal treatment | |  |  |  |  |
| Confirmation of subjective and objective symptoms | |  |  |  |  |
| Questionnaire survey on QOL | |  |  |  |  |
| Clinical tests | Blood testsb |  |  |  |  |
| Blood biochemistry  testsc |  |  |  |  |
| Periodontal examination | |  |  |  |  |

Open circles () indicate measures that will be performed prior to dental intervention. Black circles () indicate measures that will be performed after dental intervention.

aPatient characteristics indicate characteristics routinely noted in medical care, such as age, sex, past medical history, and complications.

bBlood tests indicate the same tests performed during regular medical examination.

cBlood biochemistry tests indicate the same tests performed during regular medical examination. In addition, factors associated with oxidative stress will be assessed to confirm the relationship between oral health and whole body status.

9. Discontinuation criteria

- 1. A subject asks to stop participating in the study or withdraws consent.
  2. It is found after enrollment that eligibility requirements are not fulfilled.
  3. Continuation in the study is difficult due to exacerbation of complications.
  4. A subject is discovered to be pregnant.
  5. The entire study is discontinued.
  6. Dental treatment is found to be necessary for a subject in the oral hygiene instruction group after assignment.
  7. A physician determines that discontinuation is advisable for some other reason.

10. Handling when an adverse event occurs

(1) Response to patients when an adverse event occurs

When an adverse event that requires treatment occurs in a subject, the subject will be notified and appropriate medical care for the adverse event will be provided.

(2) Report of a serious adverse event

If a serious adverse event occurs or there is concern of such an event occurring, a report will be made immediately to the Hospital Director of Okayama University Hospital.

11. Report of deviation from protocol

The following matters are provided in accordance with GCP:

- The principal investigator and co-investigators will not deviate from or make changes to the study protocol before obtaining approval from the Hospital Director based on advance review of the Ethics Committee.
- The principal investigator and co-investigators may deviate from or change the study protocol before obtaining advance approval from the Ethics Committee for compelling reasons in order to avoid an emergency. In such cases, the principal investigator or a co-investigator will submit the details regarding the deviation or change and the associated reasons, together with a proposal for revision of the study protocol if necessary, to the Ethics Committee without delay, and approval from the Ethics Committee and Hospital Director will be obtained.
- In cases of deviation from the study protocol, the principal investigator or a co-investigator will record all items of deviation and the reasons for them.

12. Completion, discontinuation, or cessation of study

(1) Study completion

At the completion of the study, the principal investigator will submit a study completion report to the Hospital Director without delay.

(2) Study discontinuation or cessation

The principal investigator will consider whether or not to continue the study in the event of either of the following:

1) Recruiting subjects is difficult and reaching the planned number of subjects is judged to be unlikely.

2) The Ethics Committee asks for changes to be made in the protocol or other matters, and those changes are judged to be difficult to make.

When a decision is made to discontinue or cease the study, a report to that effect together with the reason will be made in writing to the Hospital Director without delay.

13. Study period

From March 1, 2014 to March 31, 2016.

14. Data aggregation and statistical analysis

Data analysis will be conducted from the following observations:

1) Role of plaque control instruction in type 2 diabetes patients: The significance of plaque control instruction will be investigated from a comparison between the start of the study and the time of reassessment in the oral hygiene instruction group, including its effect on QOL.

2) Significance of periodontal treatment: The effects of periodontal treatment in type 2 diabetes patients will be discerned from a comparison of the oral hygiene instruction group and the non-surgical periodontal treatment group.

15. Target patient number and rationale

The target patient number is 20 for each group (40 patients total).

The number of patients is calculated to be 20 based on analysis of the serum HbA1c level in a previous study (see reference) on periodontal treatment in diabetes patients. To determine the sample size when the *t*-test is used, calculations were performed using SPSS Samplepower (IBM, Tokyo, Japan). Under the conditions of α=0.05 and β=0.20, with a two-tailed *t*-test, the predicted HbA1c level was 7.31% in the oral hygiene instruction group and 6.51% in the non-surgical periodontal treatment group. With an assumed standard deviation of 0.8, significance was hypothesized when the mean serum HbA1c differed by 0.8% as a result of periodontal treatment. As a result, 17 patients are needed for the study. Assuming a 15% dropout rate, the number is set at 20 patients.

16. Subjects’ rights, safety, and disadvantage

(1) Human rights (protection of privacy)

Subject data are coded and test results are provided to the person conducting the analysis at Okayama University so that individual subjects cannot be identified. To combine the data from the examination table, questionnaire, and each test, the same symbols are given to the same subject being examined. After the study has been completed, these data will be destroyed.

(2) Patient safety, disadvantage

Health insurance and other measures needed to compensate for health damage to subjects are not adopted.

Reason: There is the possibility only of slight pain when blood is taken. No damage to health is foreseen.

17. Cost to patients

Within the range of regular medical examination.

18. Expected benefit from participating in clinical study, and possible risks

A benefit from participating in this study is that subjects are given a 2,000 yen QUO card as remuneration each time they undergo medical examinations. A disadvantage is that each test takes time. There is no risk.

19. Compensation for damage to health

Health insurance and other measures needed to compensate for health damage to subjects are not adopted.

Reason: This study is performed within the range of regular medical examination, and no damage to the subjects’ health is foreseen.

20. Correspondence with GCP and Helsinki Declaration

This study will be conducted in accordance with GCP and adhere to the principles laid down in the Helsinki Declaration (2008 revision).

21. Storage of records

The principle investigator will keep all required documents related to conducting this study (copies of application forms, correspondence from Hospital Director, copies of all applications and reports, subject identification code list, consent forms, copies of case reports, and other documents or records needed to guarantee the reliability of data) and dispose of them after the study has been published.

22. Publication of study results

The study results will be compiled in a report by April 30, 2016, and reported to the Hospital Director. The study results will also be used in journal publication(s) and conference presentation(s). When the study results are made public, personal information that could be used to identify individual subjects will not be disclosed.

23. Research organization

Affiliation: Department of Preventive Dentistry, Okayama University Graduate School of Medicine, Dentistry and Pharmaceutical Sciences

Title: Professor

Name: [name]

Affiliation: Department of Public Health, Okayama University Graduate School of Medicine, Dentistry and Pharmaceutical Sciences

Title: Professor

Name: [name]

Affiliation: Department of Nephrology, Rheumatology, Endocrinology, and Metabolism, Okayama University Graduate School of Medicine, Dentistry, and Pharmaceutical Sciences

Title: Associate Professor

Name: [name]

Affiliation: Preventive Dentistry, Okayama University Hospital

Title: Lecturer

Name: [name]

Affiliation: Preventive Dentistry, Okayama University Hospital

Title: Lecturer

Name: [name]

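### The first periodontal examination comes after allocation, in subjects who know their arm, which needlessly exposes the secondary baselines and allows avoidable early exits from the control arm

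*Protocol*

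**What the plan says.** Section 6(2) describes the start of the study as a sequence. Patients who consent in the diabetes department are sent to the preventive dentistry clinic. Then "One member of the research group will separate patients into two groups", with the note that "the patients will be asked not to inform the examiners of the group to which they are assigned". The next step is "Thereafter, two dentists blinded to the group assignments will conduct periodontal examinations", and after that "Other dentists will then be in charge of oral hygiene instruction and periodontal treatment".

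The same section sets the examination times (the last figure is also in months): "Some of the above examinations will be performed a total of three times: at the start of the study, after 3 months, and after 6". Section 6(10) stratifies the allocation: "adjustments will be made according to baseline serum HbA1c (≥8% and <8%), whether a patient is receiving insulin treatment", together with the types and number of drugs. No dental measure is a stratification factor.

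The legend of the schedule table in section 8 separates measures taken before dental intervention from those taken after it. It does not mention allocation.

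Section 9 lists two discontinuation criteria that matter here. Item 2 is "It is found after enrollment that eligibility requirements are not fulfilled". Item 6 is "Dental treatment is found to be necessary for a subject in the oral hygiene instruction group after assignment".

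**The concern.** Baseline measures are normally completed before the arm is known, so that neither the subject nor the examiner can be influenced by it. Here the arm is disclosed first. Three consequences follow.

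- **Periodontal baseline.** The examiners are masked, but at week 0 that masking depends on subjects not mentioning their arm. Before allocation there would be nothing to mention.
- **QOL baseline.** QOL is self-reported, is a secondary endpoint (section 7), and its change is part of the study purpose (section 2). If the first questionnaire is completed after disclosure, the answer may depend on the arm, and the change from baseline inherits that.
- **Early exits.** If the first study dental examination shows a need for treatment, the subject has already been assigned. Item 6 then offers a route to discontinuation in one arm only. The same finding before allocation could be dealt with without losing a randomised subject.

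**Working it through.** **1. Order of events (sections 6(2) and 8).**

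| Step | Text relied on | Arm known to subject? |
|---|---|---|
| Consent, referral to dental clinic | 6(2) | No |
| Allocation from random-number table | 6(2), 6(10) | Becomes known |
| Periodontal examination by masked dentists | 6(2), next in sequence | Yes |
| Instruction and treatment by other dentists | 6(2), next in sequence | Yes |

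The examination in the third step precedes instruction and treatment, so it must include the start-of-study examination. The request for silence presupposes that subjects know their arm. No other section places a periodontal examination before allocation, and the section 8 legend is satisfied by any time before dental intervention, so it does not correct the order.

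**2. Which baselines are exposed.**

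- *HbA1c: no.* It is a stratification factor, so a value must exist before allocation, and a laboratory value does not respond to learning the arm.
- *Periodontal measures: yes, in a limited way.* They follow disclosure, but the examiners are masked and calibrated.
- *QOL: possibly.* The sequence in section 6(2) covers the periodontal examination only. The order of questionnaire and allocation is not fixed anywhere.

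**3. Which exits the order can create.** Section 4 contains no criterion on periodontal status or dental need; the only dental exclusion is being under dental treatment already. The first examination could therefore trigger item 2 only through the open investigator-judgement exclusion, which is a weak route. Item 6 is the more direct one. It does not name the baseline examination, but nothing prevents a finding there from triggering it.

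**4. Scale.** The plan's own figure first (section 15: difference 7.31 − 6.51 = 0.80, SD 0.8, two-sided α 0.05, power 0.80):

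- Normal approximation: n = 2(1.960 + 0.842)² × (0.8/0.8)² = 15.7, so 16 per group.
- Exact t-test: 16.7, so 17 per group, with power 0.807.
- Dropout: 17/(1 − 0.15) = 20 per group. The stated 17 and 20 reproduce.

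One exit is 1/20 = 5% of an arm, and the 15% allowance is 0.15 × 20 = 3 subjects. As an illustration, assume 17 of 20 remain in the treatment arm and that the lost control subjects provide no outcome. Power then comes from the noncentral t with noncentrality (0.8/0.8)/√(1/n₁ + 1/n₂) and n₁ + n₂ − 2 degrees of freedom:

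| Controls lost of 20 | Controls left | Noncentrality | Power |
|---|---|---|---|
| 3 | 17 | 2.92 | 0.807 |
| 5 | 15 | 2.82 | 0.780 |
| 8 | 12 | 2.65 | 0.725 |

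Selective loss can be illustrated in the same way. Suppose the fraction f of controls with the greatest dental need is lost to the analysis, and dental need correlates ρ with HbA1c. The control mean then shifts by −0.8 × ρ × φ(c)/(1 − f), where c is the (1 − f) normal quantile. For f = 0.1 and ρ = 0.1 this is −0.8 × 0.1 × 0.195 = −0.016. For f = 0.3 and ρ = 0.5 it is −0.8 × 0.5 × 0.497 = −0.199. The direction would narrow the planned 0.8-point difference.

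Both f and ρ are assumptions, as are the loss counts. The protocol gives none of them, and only the exits found at week 0 would be due to the order of steps.

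**The case against.** The primary endpoint is untouched, and that stands. A reader might infer from the sequence that every baseline is compromised; the stratification by HbA1c rules that out.

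The periodontal examiners are masked and calibrated to a kappa above 0.8, and tooth number, pocket depth and attachment level will not change because a subject has just learned the arm. This largely stands. What remains is an avoidable dependence on subjects' silence. The same dependence exists at months 3 and 6 whatever the week-0 order, so the gain is confined to one visit.

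The QOL problem is not stated in the text. This also stands: the protocol leaves the order open, so the defect is that exposure is permitted, not that it is prescribed.

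A reader might also infer that subjects will be excluded from the analysis after randomisation. Section 9 does not say so. It speaks of discontinuation, and the handling of discontinued subjects may be set out in an analysis plan that is not at hand. Nor does item 6 name the baseline examination: the need may appear at any time over six months, and its one-arm wording is a separate matter that reordering does not cure.

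Finally, three exits using up the allowance is arithmetic that would hold in any trial with these numbers. It is not a forecast. None of this answers the core point: the order is set by the protocol, it is the less protective one, and nothing in the document requires it.

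**Conclusion.** The point holds in limited form. Section 6(2) puts the first periodontal examination after allocation, in subjects who know their arm, and the section 8 schedule does not correct this. The exposure covers the baseline periodontal measures, possibly the baseline QOL questionnaire, and those exits under item 6 that a week-0 finding could prompt in the oral hygiene instruction group.

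The size of any bias or loss cannot be derived from the document; the figures above are illustrations under assumed loss rates and correlations. The conclusion rests on reading section 6(2) as a chronological order, which its wording supports and no other section contradicts. The document does not support the stronger conclusions that baseline HbA1c is biased, that subjects will be removed from the analysis, or that a known share of the dropout allowance will be lost at week 0. This is a cheap improvement to the secondary baselines and to early retention, not a threat to the primary comparison as documented.

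**What to change.** Reword section 6(2) and the section 8 schedule so that week 0 runs in this order: consent; HbA1c available for stratification; periodontal examination; QOL questionnaire; confirmation of eligibility; and only then allocation and disclosure of the arm to the subject. State in the schedule legend that the baseline measures precede allocation, not only dental intervention.

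The visit, staff and measurements stay the same. The cost is that a few consented subjects may be found unsuitable before allocation and need replacing to reach 40, which matters somewhat because section 12(2) already names recruitment difficulty as a reason to reconsider the study.

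The change does not remove exits under item 6 that arise after week 0, nor the reliance on subjects' silence at months 3 and 6. The one-arm wording of item 6 is for the authors to reconcile separately.

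### Non-disclosure of the arm is asked only towards the dental examiners, not the diabetes clinic staff, whose treatment changes can move the primary endpoint, HbA1c

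*Protocol*

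**What the plan says.** Section 7(1) makes serum HbA1c the primary endpoint. Section 6(2) places its measurement in ordinary care: "Blood tests are routinely conducted as part of regular medical examination in the Nephrology, Diabetology and Endocrinology Department". Visits to that department and to the dental clinic are to fall on the same day.

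Entry requires a patient to be "Currently receiving treatment for type 2 diabetes" (Section 4); stable therapy is not required. For the study period, Section 6(2) has one provision on therapy: "In cases where there is a change in diabetes treatment during the study period, the details will be recorded". Section 6(6), on concomitant medication or therapy, is marked as not applicable.

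On masking, Section 6(2) states that "two dentists blinded to the group assignments will conduct periodontal examinations" and that "the patients will be asked not to inform the examiners of the group to which they are assigned". The second statement presupposes that subjects know their arm. No statement covers the physicians or other staff who manage the diabetes.

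Section 6(10) stratifies allocation on baseline HbA1c (8% or above against below 8%), insulin treatment, and types and number of drugs (two or fewer against three or more).

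**The concern.** The protection against knowledge of allocation sits on the secondary endpoints. The periodontal examiners do not produce the HbA1c value. The staff who can change diabetes treatment can influence it, and nothing in the protocol limits what they may learn about the arm.

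The route to bias is simple. A subject mentions the dental group at a diabetes visit, or a member of the research group does. Treatment is then changed, or left alone, partly because of that knowledge. The assay faithfully records the result, and the comparison of arms in Section 14 attributes it to periodontal treatment. More intensification in the instruction arm would hide an effect; more in the periodontal treatment arm would create or exaggerate one. The direction cannot be predicted from the protocol.

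This has to be settled in the design. An analysis can describe treatment changes after the event, but it cannot restore masking lost during conduct. Section 2 intends the results to support insurance coverage of periodontal treatment, so a clear attribution of any HbA1c difference matters.

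**Working it through.** **Inputs from Section 15.** Two-sided t-test, α = 0.05, β = 0.20; predicted HbA1c 7.31% and 6.51%, a difference of 0.8; SD 0.8; 17 evaluable per arm; 15% dropout; 20 enrolled per arm.

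**Reproducing the plan's figure.** The standardised difference is 0.8 / 0.8 = 1.0. The two-sample t-test then needs 16.71, so 17 per arm, and power at 17 is 80.7%. Allowing for dropout, 17 / 0.85 = 20. The stated sample size reproduces, with almost no margin in the evaluable number.

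**Assumed inputs, not in the protocol.** Let *q* be the excess fraction of one arm whose treatment is intensified because the arm is known, and *e* the HbA1c drop in each such subject. The mean difference between arms shifts by *b* = *q* × *e*.

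- *q* = 0.20, *e* = 0.5: *b* = 0.10
- *q* = 0.20, *e* = 1.0: *b* = 0.20
- *q* = 0.30, *e* = 1.0: *b* = 0.30

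**Power and rejection rate.** With *n* = 17 per arm there are 17 + 17 − 2 = 32 degrees of freedom, and the non-centrality is (difference / 0.8) × √(17/2) = (difference / 0.8) × 2.915. If the excess falls in the instruction arm, a true difference of 0.8 becomes 0.8 − *b*. If periodontal treatment has no effect, the expected difference is *b* in one direction or the other.

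| Shift *b* | Remaining difference | Non-centrality | Power | Non-centrality, no true effect | Two-sided rejection rate, no true effect |
|---|---|---|---|---|---|
| 0 | 0.80 | 2.915 | 80.7% | 0 | 5% |
| 0.10 | 0.70 | 2.551 | 69.6% | 0.364 | 6.4% |
| 0.20 | 0.60 | 2.187 | 56.4% | 0.729 | 10.9% |
| 0.30 | 0.50 | 1.822 | 42.4% | 1.093 | 18.6% |

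**Sensitivity of the illustration.** If all 20 per arm were evaluable, power would be 86.9% with no shift, 76.9% at a shift of 0.10 and 48.7% at 0.30. The table holds the SD at 0.8, although treatment changes in only some subjects also add spread. If 10% of the other arm were intensified as well, power at 17 per arm would be 67.2% for *q* = 0.20, *e* = 0.5 and 35.1% for *q* = 0.30, *e* = 1.0.

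**The case against.** The strongest reply is that the pathway is hypothetical. Section 6(2) gives allocation to one member of the research group, and nothing says that diabetes physicians are told the arm or that they would act on it. HbA1c is a laboratory value, so there is no unmasked measurement. Entry therapy is balanced by stratification and changes are captured. All of this stands, and it makes the point conditional. It does not close the gap: stratification does nothing for changes after randomisation, recording does not prevent them from depending on the arm, and an objective assay registers a drug effect as readily as a dental one.

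The magnitude is also fairly challenged. The protocol gives neither *q* nor *e*. The worst case needs about five extra intensified subjects (0.30 × 17 = 5.1), each falling by a full point. The planning difference comes from a previous study, and whether it already reflects treatment changes is unknown, so subtracting a shift from it may count the same thing twice. The figures show sensitivity and are not a forecast.

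Three stronger readings are tempting, and the documents do not support them.

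- A reader might infer that any intensification in subjects with higher HbA1c biases the trial. If the staff do not know the arm, such changes follow from randomised care. They may narrow the difference, but they are not bias, and masking the clinic would not remove them.
- A reader might infer that the recorded changes will never be analysed. Section 14 does not mention them, but such rules commonly sit in a statistical analysis plan, which is not at hand.
- A reader might take the entry in Section 6(6) as a proven contradiction of 6(2). It stands in a run of drug-trial headings, 6(4) to 6(9), all marked the same way, and can mean that the study imposes no restriction on therapy. It needs reconciling for clarity and is not evidence of bias.

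**Conclusion.** The gap in scope is real. The protocol asks for non-disclosure where it protects secondary endpoints and not where it would protect the primary one. Whether bias follows depends on two things the protocol does not establish: that diabetes clinic staff learn the arm, and that treatment changes then differ because of it. If both happen, the direction is open. For an assumed imbalance of 0.1 to 0.3 HbA1c points, at 17 per arm and SD 0.8, the consequence is a rejection rate of up to 18.6% without a true effect, or power as low as 42.4% for the planned difference. I would class the change as a cheap improvement: it removes an avoidable exposure but corrects no error in the plan's own figures.

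**What to change.** 1. In Section 6(2), extend the existing request so that subjects also do not tell diabetes clinic staff their group, and state that the research group does not pass the allocation to those staff except for safety need. Section 23 lists a member from the nephrology, endocrinology and metabolism department, so the wording should make clear who in the research group may see the allocation.
2. Reconcile the entry in Section 6(6) with the statement in 6(2) that treatment changes are recorded. This can be done without setting any rule for diabetes care, and none is proposed here.
3. Report the proportion of subjects with a treatment change by arm, as a descriptive check on whether the arms were managed differently. The changes are already to be recorded.

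The cost is a few sentences and one descriptive table. The clinic must avoid casual disclosure, and non-disclosure by subjects who know their arm will be imperfect, especially with same-day visits. The change therefore reduces the risk and does not abolish it; the table by arm helps to show whether the arms were managed differently.
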